### Study flowchart

2.9

The study flowchart is presented in Fig. 1.

**Figure 1 F1:**
[figure not shown]
The flow diagram of the GRANTISS study.

### Data and safety monitoring

2.10

An independent DSMB comprised of 3 clinical experts, 1 competent nurse, and 1 statistician will monitor the progress and safety of the trial. When the trial is actively recruiting, the DSMB will be responsible for reviewing nonintervention data every 6 months, including the implementation of standard care measures and conventional treatments, dropout events, adverse events, and serious adverse events. The committee has the right to suspend the trial at any point to ensure that it is implemented scientifically and in an ethically appropriate manner.

### Sample size

2.11

According to previous clinical experience, the mortality rate of sepsis in this study center is about 33%. Our sample size was calculated to detect a 20% difference in mortality on day 28 between the 2 groups with a 2-tailed test, a = 0.05, β = 0.2 (power = 80%). Considering some factors such as shedding and loss of follow-up, an additional 15% of the sample size was added, resulting in a total of 154 patients, 77 in the control group, and 77 in the treatment group.

### Statistical analysis

2.12

Statistical analysis plan has been reviewed and approved by professional medical statisticians from the Clinical Trial Committee of Zhujiang Hospital (2018LX0003-GY).

#### Statistical analysis data set

2.12.1

The analysis will be based on a modified intent-to-treat population in which patients who have undergone at least 1 study intervention and one assessment can be included in the analysis.

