### Randomization allocation concealment

2.4

Patients who are eligible for enrollment will be randomized, and they will be assigned with an equal chance to the granisetron and placebo control group, with a 1:1 ratio between the treatment and control groups. The random sequence was generated by an independent Data Security Management Board (DSMB) using Stata 13, and the randomized cards were made by the relevant personnel according to the random sequence. Each random group card was marked with a patient's enrollment group and loaded into a customized sealed envelope. The randomly grouped block lengths will not be made public until the trial is completed. After successful recruitment, the clinical screeners will open the envelope and complete the random assignment based on the randomized information. If more than 1 patient is successfully recruited at the same time, the order of randomization for patients is determined based on the registered time of ICU admission.

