### Blinding

2.5

The trial used a single-blind design in which the subjects, subject relatives, and relevant statisticians will remain blind to the trial grouping. To achieve this process, the control group will use normal saline as a placebo with the same appearance as granisetron and use same 50 mL syringes as drug containers and use the word “GRAN” as the drug infusion label.

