### Interventions

2.6

The recruited patients will begin the trial intervention within 8 hours after randomization. Patients in the granisetron-treated group will receive granisetron 3 mg (PKU HealthCare Corp, Ltd) diluted to 25 mL with 22 mL of saline and intravenously administered within 10 minutes. Patients in the placebo group will receive 25 mL of normal saline and administer it intravenously within 10 minutes. The trial intervention will be administered at a frequency of 8 hours, with a course of treatment of 4 days or ICU discharge, whatever comes first. Considering the fluctuation of vital signs such as body temperature and blood pressure at different time points in 1 day, to avoid the influence of the abovementioned confounding factors on the trial results, it is stipulated that the trial intervention for each patient will be held at 12:00, 20:00, and 04:00. In addition to the trial intervention, patients will receive routine standard care and routine sepsis treatment according to the 2016 International Management Guidelines for Sepsis,^[7]^ including but not limited to the use of antibiotics, venous fluid resuscitation, use of blood products, enteral or parenteral nutrition, prevention of deep vein thrombosis, and supportive treatment for organ dysfunction. All treatments except study interventions will be determined by the treating physician and will be noted in detail in patients’ medical records.

For patients who may require using antiemetics, any antiemetics that act on 5-HT receptors should be avoided, but other classes of antiemetics such as metoclopramide may be used. Additionally, in the treatment of patients with sepsis, some liver-protective drugs such as reduced glutathione are often used to reduce septic liver damage; because the role of granisetron for liver function protection in clinic is not certain, the use of such drugs to alleviate organ dysfunction by the treating physician will be allowed, but the name, frequency, and dosage of the drug used should be accurately recorded.

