### Data collection

2.7

The patients enrolled in the group will receive clinical or laboratory assessments (Table 1) during the screening period, the drug infusion period, on the first day after the end of trial interventions, and on the 28th day after enrollment. Before treatment (D0; screening period), the following indicators should be evaluated: pathogen culture results, the level of blood 5-HT, acute physiology and chronic health evaluation (APACHE II) scores, and SOFA scores. Before treatment (D0; screening period), on the third day of treatment (D2), and on the first day after treatment (D4), the following indicators will be measured: immune function indicators (white blood cell count, peripheral lymphocyte count, CD4+ and CD8+ T-cell count), renal injury indicators (Cys C), inflammation Indicators (the level of IL-6, CPR, ESR, SOD), and infection indicators (the level of serum PCT, fungi (1,3)-beta-D-Glucan, galactomannan antigen). Daily assessment indicators include the following: liver injury indicators (the level of ALT, AST, total bilirubin, direct bilirubin), the level of blood lactate, renal injury indicators (the level of Cr, BUN), lung injury indicators (oxygenation index, not applicable during extracorporeal membrane oxygenation (ECMO) support), fluid balance, vasoactive drug dose, urine volume, SOFA scores, and concomitant medications that may affect the outcome. Other indicators are the duration of organ function replacement therapy including continuous renal replacement therapy (CRRT), ECMO and mechanical ventilation, the incidence of new dysfunction, ICU stay time, ICU mortality, and 28-day mortality. Safety indicators include adverse reactions and the incidence of serious adverse events. Among them, the 28-day survival information of patients will be obtained by telephone follow-up. For dropout events, the causes will be recorded in detail and these patients will also be followed up. All the laboratory outcomes will be taken from the Central Laboratory of Zhujiang Hospital, and all the indicators needed to calculate the APACHE II score and SOFA score will also be recorded in detail. Furthermore, during the course of treatment, any out-of-plan evaluations of the above indicators by the treating physicians also will be collected. All of the above data will be collected by highly trained clinical observers.

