#### Primary outcome

2.8.1

The primary outcome measure is the all-cause mortality rate at 28 days after enrollment.

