#### Primary outcome

2.12.8

The 28-day all-cause mortality difference will be compared using Pearson chi-square test and logistic regression analysis with adjustment for the variables may affect mortality rate.

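### The stated analysis set for 28-day mortality leaves out randomised patients who received no dose, so deaths before the first dose are lost from the primary comparison

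*Protocol article*

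**What the plan says.** Section 2.12.1 of the protocol article (Statistical analysis data set) bases the analysis on a modified intention-to-treat population in which "patients who have undergone at least 1 study intervention and one assessment can be included in the analysis". It is the only analysis set in the article. Section 2.12.8, on the analysis of the primary outcome, gives the tests but no separate population: "The 28-day all-cause mortality difference will be compared using Pearson chi-square test and logistic regression analysis".

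The endpoint itself runs from entry to the trial, not from first dose: "The primary outcome measure is the all-cause mortality rate at 28 days after enrollment" (section 2.8.1).

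Four other statements bear on who drops out under the rule:

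- Start of treatment (section 2.6): "The recruited patients will begin the trial intervention within 8 hours after randomization". Doses are tied to the clock: "the trial intervention for each patient will be held at 12:00, 20:00, and 04:00".
- Allocation (section 2.4): "the clinical screeners will open the envelope and complete the random assignment based on the randomized information".
- Blinding (section 2.5): "the subjects, subject relatives, and relevant statisticians will remain blind to the trial grouping". Treating physicians, screeners and observers are not on this list.
- Follow-up (section 2.7): "For dropout events, the causes will be recorded in detail and these patients will also be followed up". Survival at day 28 is obtained by telephone.

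**The concern.** Randomisation makes the arms comparable at the moment of allocation. A rule that then removes patients according to what happens afterwards keeps that comparability only if removal is unrelated to both outcome and arm. Here neither is assured.

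- **Relation to the outcome.** One reason for never receiving a dose is death before it is due. Such a patient has met the primary endpoint and is then taken out of its analysis.
- **Relation to the arm.** The usual defence of a dosed-only set is that nobody who influences the first dose knows the allocation. The article does not secure this: the clinical screeners learn the arm, and the treating team is not listed as blind.

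The wording also leaves open whether the one assessment must come after a dose. On that reading, deaths soon after dosing would be lost as well. What is at stake is bias in the mortality difference, in either direction, in a trial that expects few deaths.

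**Working it through.** **1. Inputs.** From section 2.11: control mortality 33%, a 20% difference, two-sided 0.05, power 80%, a 15% addition, and 77 patients per arm (154 in total). The article gives no expected number of undosed patients, so the number of excluded deaths, k, is an assumption.

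**2. The plan's own figure.** Reading the difference as 20 percentage points (33% against 13%), the unpooled normal formula gives

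n = (1.960 + 0.842)² × (0.33×0.67 + 0.13×0.87) / 0.20² = 7.849 × 0.3342 / 0.04 = 65.58 per arm.

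Dividing by 0.85 gives 77.15 per arm, or 154.3 in total, which matches 154. A relative 20% reduction (33% to 26.4%) would need 752 per arm before inflation, so the absolute reading is the one used. Expected deaths: 77×0.33 + 77×0.13 = 35.4.

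**3. Who the rule removes.** Dosing slots are 8 hours apart, so a wait of up to 8 hours is built in. There are two readings of the assessment condition:

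- *The baseline (D0) assessment counts.* Section 2.7 schedules one for every patient before treatment. The condition then removes almost nobody, and exclusion acts through the dose condition alone.
- *A post-dose assessment is required.* Patients who die after a dose but before that assessment are removed too.

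**4. False-positive rate over an assumed range.** Suppose there is no true effect, mortality is 33% in both arms, and k eventual deaths are lost from the granisetron arm only. Its apparent mortality is (25.41 − k)/(77 − k), where 25.41 = 0.33×77. The error rates come from exact binomial enumeration of the uncorrected Pearson test, 77 control patients against 77 − k.

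| k | Apparent granisetron mortality | Bias (points) | False positive favouring granisetron | Two-sided error |
|---|---|---|---|---|
| 0 | 33.0% | 0 | 2.5% | 5.1% |
| 1 | 32.1% | −0.9 | 3.3% | 5.2% |
| 3 | 30.3% | −2.7 | 5.6% | 6.6% |
| 5 | 28.3% | −4.7 | 9.0% | 9.5% |

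**5. Single tables** (control against granisetron, χ² = N(ad − bc)² / product of the four margins).

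- Borderline, all randomised, 25/77 vs 15/77: χ² = 154×770² / (77×77×40×114) = 3.38, p = 0.066.
- One granisetron death dropped, 25/77 vs 14/76: χ² = 153×822² / (77×76×39×114) = 3.97, p = 0.046. Two dropped (13/75): p = 0.031.
- The opposite direction, 25/77 vs 14/77: p = 0.042. One control death dropped (24/76): p = 0.055.
- Balanced loss from the first table, one death per arm (24/76 vs 14/76): p = 0.061. Two per arm (23/75 vs 13/75): p = 0.056.
- At the design effect, 25/77 vs 10/77: p = 0.004. Two granisetron deaths dropped (8/75): p = 0.001.

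**The case against.** The case for leaving the rule alone has several fair parts.

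- **The exclusion may be small.** If the baseline assessment counts, only deaths or non-starts within at most 8 hours are lost. The eligibility criteria already exclude some patients likely to die at once, such as those with limited care, prior resuscitation, uncontrolled bleeding or cerebral hernia. This stands, and it is why no size can be claimed beyond an assumed range.
- **Clinician knowledge is not stated.** A reader might infer that the treating team knows the arm and withholds first doses accordingly. The documents do not support that. The saline looks the same, the syringes match and both carry a common label; nothing describes arm-driven non-starts. What stands is narrower: clinicians are not listed as blind and screeners see the allocation, so the safeguard that a dosed-only set relies on is not in place.
- **Other analyses may be planned elsewhere.** The article refers to a reviewed analysis plan that is not shown. The absence of a supporting all-randomised analysis is therefore not part of this point; the stated choice of main set is.
- **Follow-up of undosed patients is not explicit.** The article promises follow-up of dropouts but does not say that a patient who was never dosed is one. This stands and is taken into the fix.

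None of this answers the core problem. A death before the first dose meets the endpoint definition and is removed by the analysis set, whoever knows the arm.

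**Conclusion.** The point holds in a limited form. Section 2.12.1 fixes a set that can drop primary-endpoint events after randomisation, and the design does not ensure that this is independent of arm. The endpoint, counted from enrolment, and the analysis set, conditional on dosing, do not fit together.

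The size is unknown because the number and direction of exclusions are unknown. Under the one-sided assumption of 1 to 5 lost granisetron deaths, no true effect and 33% mortality, the false-positive rate in favour of granisetron rises from about 2.5% to between 3.3% and 9.0%. Losses from the control arm would bias the other way.

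A reader might conclude from the roughly 35 expected deaths that a few exclusions would decide the trial. That goes too far. The change from p = 0.066 to below 0.05 needs a borderline table, which has 40 deaths and not 35, and exclusions in one arm only. Balanced losses of one or two deaths per arm did not cross 0.05, and neither did the result at the design effect. The case for change rests on the principle and the low cost of the remedy, not on a demonstrated large bias.

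**What to change.** In section 2.12.1, state that 28-day mortality is analysed in all randomised patients, in the arm assigned, regardless of dosing or assessment. State also that day-28 vital status will be sought for everyone randomised, including those never dosed. Keep the dosed set for safety and as a sensitivity analysis, and say there whether its one assessment must follow a dose.

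The cost is a short edit, plus the planned day-28 telephone call for any undosed patients not already covered. The sample size stays at 154. Under the design assumptions, the pooled formula gives power of 84.6% with all 77 per arm analysed, against 78.6% with 66 per arm, so retaining patients does not hurt precision. The downside is slight dilution of the effect by any patients who were never dosed.

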#### Basic statistical principles

2.12.2

All statistical inferences will be performed using a 2-sided test unless otherwise specified. The statistically significant test level is at 0.05, and the interval estimate for the parameters used a 95% confidence interval. Statistical inference will be performed using the parameter method as much as possible. When the data does not satisfy the parameter method condition, the data conversion method can be used to satisfy the condition. If it is still not satisfied, a nonparametric method can be considered.

#### Processing of missing data

2.12.3

Analysis based on modified intent-to-treat population sets using the last observation carried forward method, that is, the case where the entire treatment process is not observed but rather the last observation data is transferred to the final result of the test

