#### Secondary outcome

2.8.2

The secondary outcome indicators mainly include the following aspects:

Requirements for organ function support: the duration of organ function replacement therapy including CRRT, ECMO, and mechanical ventilationImprovement of organ function: the changes in SOFA score; creatinine, transaminase, and cystatin after interventions completion; lactate clearance after interventions completion; and the incidence of new organ dysfunctionImprovements in infection indicators: the changes in PCT after interventions completion, PCT clearance after interventions completion, and changes in fungi (1,3)-beta-D-Glucan and galactomannan antigen after interventions completion.Improvement of inflammatory indicators: the changes in IL-6, ESR, SOD, and CRP after interventions completionImprovement of immune function indicators: the changes in lymphocyte count, white blood cell count, and CD4+ and CD8+ T cell count after interventions completion.The incidence of new organ dysfunction: the incidence of new acute liver injury, kidney injury, and lung injury. New organ failure refers to organ failure that occurs after enrollment.Other indicators: ICU length of stay (LOS).Additionally, we will also collect blood 5-HT levels before and after completion of the treatment to determine if there is a correlation between 5-HT levels and the prognosis of sepsis.

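### Last observation carried forward is the only stated missing-data rule, with no exception for 28-day mortality or for death before the post-treatment assessment

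*Protocol article*

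**What the plan says.** Section 2.12.3 (Processing of missing data) is the whole of the stated rule: "Analysis based on modified intent-to-treat population sets using the last observation carried forward method", so that "the last observation data is transferred to the final result of the test". No outcome is excepted, and death is not mentioned.

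Four other places determine what the rule does:

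- **Analysis set (2.12.1):** "patients who have undergone at least 1 study intervention and one assessment can be included in the analysis". A known day-28 status is not required.
- **Primary outcome (2.8.1) and its analysis (2.12.8):** "The primary outcome measure is the all-cause mortality rate at 28 days after enrollment"; "The 28-day all-cause mortality difference will be compared using Pearson chi-square test and logistic regression analysis". This is a binary analysis with no censoring.
- **Source of the primary outcome (2.7):** "the 28-day survival information of patients will be obtained by telephone follow-up". The same section adds that dropouts are followed up too.
- **Sample size (2.11):** "Considering some factors such as shedding and loss of follow-up, an additional 15% of the sample size was added".

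For secondary outcomes, 2.8.2 uses changes after the end of treatment, for example in "creatinine, transaminase, and cystatin after interventions completion". Under 2.7, cystatin C, PCT, IL-6 and the lymphocyte counts are measured at D0, D2 and D4. SOFA, creatinine, transaminases, bilirubin and lactate are measured daily. Section 2.12.9 offers covariance analysis or a mixed linear model for repeated measures and does not say that either replaces carrying forward.

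**The concern.** Carrying forward suits neither type of endpoint here.

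For vital status, the last observation of anyone lost to follow-up is necessarily alive. The rule can therefore only hide deaths and never add them. If more patients are lost in one arm, or if those lost are sicker in one arm, the primary comparison is biased.

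For the D4 measures, the plan expects about a third of control patients to die by day 28, so some D4 values will be missing because the patient has died. Entering the last pre-death value as the post-treatment result treats death as if the patient had stayed at that level. If the arms differ in early deaths, the organ-function and biomarker comparisons are distorted.

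This is a method that the document fixes, not a detail left to a separate analysis plan.

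**Working it through.** **1. The plan's own figure.** Inputs from 2.11: control mortality 33%, a 20-point difference (so 13%), two-sided alpha 0.05, power 80%, 15% added. The arcsine formula gives h = 2(arcsin √0.33 − arcsin √0.13) = 0.486 and n = 2(1.960 + 0.842)²/h² = 66.4, so 67 per arm. Then 67 × 1.15 = 77.05, or 77 per arm and 154 in total, as stated. A 20% relative reduction (33% vs 26.4%) would need 752 per arm, so the difference is absolute.

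**2. Equal loss, unrelated to death.** Assumption: a fraction d is lost in each arm and all are carried forward as alive. The analysed rate is then p(1 − d). Power is that of the uncorrected Pearson test by exact binomial enumeration. The fair comparator is an observed-case analysis at the same loss, with 77(1 − d) patients per arm rounded to a whole number.

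| Loss d (assumed) | Analysed rates | Difference | Power, carried forward (77/arm) | Power, observed cases |
|---|---|---|---|---|
| 0% | 33.0% vs 13.0% | 20.0 | 85.4% | 85.4% |
| 5% | 31.4% vs 12.4% | 19.0 | 83.1% | 83.2% (73/arm) |
| 10% | 29.7% vs 11.7% | 18.0 | 80.6% | 81.5% (69/arm) |
| 15% | 28.1% vs 11.1% | 17.0 | 77.8% | 79.0% (65/arm) |

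The rule itself costs 0.1, 0.9 and 1.2 points of power at 5%, 10% and 15% loss. The mortality ratio is unchanged, because both rates are multiplied by the same factor. At 15% loss, 0.15 × 77 = 11.6 patients per arm are lost, and about 11.55 × 0.33 = 3.8 control and 11.55 × 0.13 = 1.5 granisetron deaths would go uncounted.

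**3. Unequal loss, no true effect.** Assumption: 33% mortality in both arms, including among those lost.

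- 5% control vs 15% granisetron loss: 0.33 × 0.95 = 31.35% and 0.33 × 0.85 = 28.05%, a false difference of 3.3 points. Exact type I error is 7.3%, against 5.1% with no loss.
- 0% vs 15%: 33.0% and 28.05%, about 5.0 points; type I error 10.2%.

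For scale, the standard error in the 5% vs 15% case is √(0.3135 × 0.6865/77 + 0.2805 × 0.7195/77) = 7.4 points, so the 3.3-point bias is a little under half a standard error.

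**4. Death before D4.** No arithmetic is needed to see the effect:

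- Marker measured at D0/D2/D4, death before D2: D0 is carried forward, and the change is exactly zero.
- Same marker, death after D2 and before D4: the D2 value is used.
- Daily marker: the last daily value is used, so any decline already recorded is kept.

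The document gives no timing of deaths. If 10% to 40% of 28-day deaths fell before D4 (assumption), 77 × 0.33 = 25.4 control deaths and 77 × 0.13 = 10.0 granisetron deaths would give 2.5 to 10.2 and 1.0 to 4.0 such patients.

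**The case against.** The strongest defence is that the protocol nowhere says a patient with unknown status is a survivor. Section 2.12.3 describes its trigger as an incompletely observed course of treatment, which fits the D0/D2/D4 measurements better than day-28 vital status. That reading is possible, but the sentence applies the method to the whole analysis set and exempts nothing. An analyst following it would carry mortality forward.

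Three stronger readings are tempting and are not supported:

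- **That 15% of day-28 statuses will be unknown.** The allowance covers shedding and loss to follow-up together, and 2.7 follows dropouts up. It is no forecast of missing vital status, and few may be missing. The 5% and 10% loss rates are likewise assumptions.
- **That carrying forward lowers power from 85% to 81% at 10% loss.** Most of that fall comes from losing patients. Against observed cases at the same loss, the rule costs about 1 point.
- **That every death before day 4 is scored as no deterioration.** SOFA, creatinine, transaminases and lactate are daily, and 2.7 also collects unscheduled evaluations. A change of exactly zero arises only for D0/D2/D4 markers with death before D2.

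It is also fair to say that sensitivity analyses may sit in a plan not shown. Their absence here is not the point; the stated rule is.

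**Conclusion.** The point stands, as something that should be fixed. As written, the rule counts a patient with unknown day-28 status as alive in a binary mortality analysis and enters pre-death values as post-treatment results.

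The size for the primary endpoint depends on how many statuses are missing and why, which the document does not say. If loss is equal and unrelated to death, the cost is about 1 point of power and a proportionate understatement of mortality in both arms. If loss is unequal or informative, there is bias between arms: 3.3 points and a type I error of 7.3% under the assumed 5% vs 15% split. With near-complete telephone follow-up, the effect on mortality would be small. For the D4 measures, the distortion grows with the number of early deaths and with their imbalance between arms, neither of which can be fixed from the document.

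**What to change.** 1. **Day-28 mortality.** State in 2.12.3 that carrying forward does not apply. Analyse observed vital status, handle the few missing by multiple imputation from baseline covariates, and add a best-case/worst-case sensitivity table.
2. **D2 and D4 measures.** Drop carrying forward and use the mixed linear model already named in 2.12.9 on the observed data. Report deaths before D4 by arm beside these results. Add a sensitivity analysis that does not score death as no change; ranking death as the worst outcome is one option among several.

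Neither step requires changing the analysis set or replacing the chi-square and logistic regression comparison. The cost is protocol and analysis-plan wording and a little programming, with no extra patients or data. The change should be made before the statisticians are unblinded.
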